### Study design and randomization

This type 3 hybrid implementation-effectiveness study will test two discrete implementation strategies for improving professional interpreter use (primary implementation outcome) and patient comprehension (secondary effectiveness outcome) in primary care. The implementation strategies—interactive web-based educational modules and access to mobile video interpreting—target different sets of barriers to professional interpreter use, an evidence-based practice [20, 21, 34, 82, 83]. Our results will therefore provide insights into how best to promote implementation of a well-studied, well-established practice known to improve outcomes but inconsistently used. As the potency of barriers may vary by provider and clinic, we will test the strategies alone and in combination, using a SMART design, with provider-level randomization.

A total of 55 providers from 3 to 5 primary care clinical organizations will be randomized 1:1 to either education or mobile video interpreting access, stratified by baseline interpreter use and clinic (phase 1; Fig. 2). Randomization will occur within REDCap, using a sequence generated by the study biostatistician and implemented by a research coordinator. After 9 months, providers with interpreter use in the top tertile (within strategy) will remain with the original strategy; those in the bottom two tertiles will be randomized 1:1 again, to continue the original strategy or to add the second strategy to the first (phase 2). After another 9 months of data collection, we will provide free access to both mobile video interpreting and educational modules to all enrolled providers and then track voluntary uptake by those not previously exposed for another 9 months (phase 3). Data collection will include *administrative data* to track interpreter use (primary outcome); *patient surveys and qualitative interviews* to determine diagnosis comprehension (secondary outcome) and communication quality; *provider surveys and qualitative interviews* to assess contextual and intrapersonal barriers and moderators; and *visit video recording* to capture additional barriers and determine fidelity of strategy implementation. We will assess each strategy’s effectiveness, alone and in combination, for improving professional interpreter use and patient comprehension. We will explore mechanisms by which these strategies work and evaluate the relative strategy-specific costs.

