#### Aim 1: Compare the effectiveness of two implementation strategies, alone and in combination, to improve use of interpretation and comprehension for patients/parents with language barriers seen in adult/pediatric primary care settings

We hypothesize that, compared to educational modules, provider access to mobile video interpreting will lead to (*H1*) greater odds of interpreter use for visits with patients/parents with language barriers (primary outcome) and (*H2*) better comprehension among patients/parents with language barriers. We also hypothesize (*H3*) that mobile video interpreting and educational modules together will yield greater odds of interpreter use than either strategy alone.

To test *H1* and *H3*, we will use assigned strategy and data collected during phases 1 and 2. Under the SMART design, comparisons of first-stage interventions, comparisons of second-stage interventions, and comparisons of the adaptive intervention with both stages can be conducted simultaneously using standard software with a technique called a “weighted and replicated” regression approach, using weighted generalized estimating equations (GEE) [66, 97]. Weighted GEE allows us to work with binary outcomes and weights and adjust for clustering within providers. Within-clinic correlations will be assessed by including clinic-specific random effects in our regression models and estimating the intra-cluster correlation coefficients. Significance of the intra-cluster correlation coefficients will be examined by comparing models with and without clinic-specific random effects using likelihood ratio tests. If no strong within-clinic correlation is detected, we will use fixed-effects regression models for their better power; otherwise, estimates and inference based on random-effects regression models will be reported. *H1* and *H3* will be tested using the Wald test and robust standard error estimates [66, 97]. Model-based estimates of odds ratio comparing education to mobile video interpreting or both will be reported, along with 95% confidence intervals [98].

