Effectiveness measures will be based on Aim 1 analyses; cost data will come from two sources. The first source is administrative, including vendor invoices and budgets for payroll. Costs that cannot be determined will be estimated with a micro-costing approach in which unit cost multipliers are applied to the quantity of each type of service or resource utilized; examples include the use of shared resources (space, office equipment) and opportunity costs experienced by clinic staff. All cost data are summed to obtain total costs [112], using an approach we have used previously [113, 114]. While mobile video interpreting-assigned providers may also have used other professional interpretation, we will assign mobile video interpreting-related costs to the mobile video interpreting and combination groups and nonmobile video interpreting interpreter costs (which would not be necessary if a clinic used mobile video interpreting only) to the education group. Interpreter costs will be based on actual usage from vendor invoices, attributed to assigned group. Education module development will be annuitized over the study period. Time costs for providers (time on modules, learning to use mobile video interpreting) and study staff (reminder emails, mobile video interpreting support) will be estimated using the mean hourly wage from the National Compensation Survey, plus fringe rates from the Bureau of Labor Statistics Employer Costs for Employee Compensation. Provider costs due to own-device use for mobile video interpreting will be estimated with hardware depreciation allowances per the US Internal Revenue Code. Costs will be inflation-adjusted to common-year dollars using the Personal Health Care Expenditure Deflator or Personal Consumption Expenditure price index [112].

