We will calculate total costs associated with each implementation strategy by summing the above costs. To test *H4a*, we will calculate the ICER for each additional interpreted clinic visit, by calculating the difference in total costs for (i) mobile video interpreting vs education and (ii) mobile video interpreting plus education vs education, and then divide by the difference in number of professionally interpreted visits for providers assigned to (i) mobile video interpreting vs education and (ii) mobile video interpreting plus education vs education. To test *H4b*, we will calculate the ICER for each additional instance of patient comprehension. To do so, we will calculate the difference in total costs for (i) mobile video interpreting vs education and (ii) mobile video interpreting plus education vs education and then divide by the difference in proportion of patients who correctly reported their diagnosis for providers assigned to (i) mobile video interpreting vs education and (ii) mobile video interpreting plus education vs education.

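### The H4b formula in Aim 3 does not give the cost per additional instance of comprehension that it names, and the H4a formula is valid only if the compared groups have equal numbers of eligible visits

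*Protocol article*

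**What the plan says.** The Aim 3 section of the Protocol article first forms a total for each strategy: "We will calculate total costs associated with each implementation strategy by summing the above costs". Both ratios use the difference between these totals as numerator, for mobile video versus education and for the combination versus education.

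- H4a: the analyst is to "then divide by the difference in number of professionally interpreted visits for providers assigned to" the groups compared.
- H4b: the target is stated as "we will calculate the ICER for each additional instance of patient comprehension", and the instruction is to "then divide by the difference in proportion of patients who correctly reported their diagnosis".

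The section does not put costs or effects on a per-visit, per-patient or per-provider base. It does say that "Effectiveness measures will be based on Aim 1 analyses". In the Aim 1 section, for H1 and H3, "we will use assigned strategy and data collected during phases 1 and 2". Under Study design and randomization, providers "will be randomized 1:1 to either education or mobile video interpreting access, stratified by baseline interpreter use and clinic". The combination first arises nine months later, when half of the providers in the lower two tertiles add the other strategy.

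**The concern.** A cost-effectiveness ratio is a cost per unit of effect only if numerator and denominator refer to the same people over the same period. In H4b the numerator is a sum over a whole group and the denominator is a mean on a 0-to-1 scale. In H4a both are sums, so both move with the number of providers, months and visits in each group as well as with the effect of the strategy.

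Aim 3 exists to help organization leaders choose a strategy. A published H4b figure labelled as cost per additional comprehending patient would be far too large. A combination figure under H4a could reflect length of exposure more than benefit.

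**Working it through.** **Inputs from the Protocol article.** 55 providers, loss of up to 9, so 46 retained; 7 visits per provider per month; 5796 visits in total and 1932 per group (Interpreter use). 216 surveys per group and a 14-point difference (Patient/parent comprehension). Two 9-month phases; top tertile continues, the rest are re-randomized 1:1 to continue or add (Study design and randomization).

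**Plan's own figure.** 46 × 7 × 18 = 5796, and 5796 / 3 = 1932. Both reproduce exactly.

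**H4b.** Let D be the difference in total cost, d the difference in proportions and N the number of patients or visits that the costs cover.

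- As written: D / d.
- Cost per additional instance: D / (N × d).
- The written form is larger by the factor N.

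The documents give no cost difference, so D = $10,000 is an assumption for illustration; the factor N does not depend on it. With d = 0.14:

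- As written: 10,000 / 0.14 = $71,429.
- N = 216: 10,000 / (216 × 0.14) = 10,000 / 30.24 = $331.
- N = 1932: 10,000 / (1932 × 0.14) = 10,000 / 270.48 = $37.

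**H4a, visits per group over phases 1 and 2.** This assumes attrition spread evenly, with 23 providers per arm.

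- Phase 1, each single strategy: 23 × 7 × 9 = 1449.
- Phase 2, each single strategy: two thirds of 23 (top tertile plus those randomized to continue) × 63 = 966.
- Phase 2, combination: one third of 23 from each arm, 15.33 × 63 = 966.
- Pooled: education 1449 + 966 = 2415; mobile video 2415; combination 966. Sum 5796. Ratio 2415 / 966 = 2.5.

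With use rates p_C (combination) and p_E (education), the H4a denominator for combination versus education is 966 × p_C − 2415 × p_E. It is positive only if p_C > 2.5 × p_E, which is impossible once education use exceeds 40%. The rates below are assumed:

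- 30% vs 35%: 338.1 − 724.5 = −386.
- 50% vs 55%: 531.3 − 1207.5 = −676.
- 50% vs 60%: 579.6 − 1207.5 = −628, although the combination is 10 points better.

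On a common base the sign is right: a 5-point gain is +48 interpreted visits per 966, or +97 per 1932.

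**Totals that scale together do not cancel the problem.** Assume 50% use in both groups, with cost per visit of $20 for education and $25 for the combination. The combination then costs more and adds nothing. The written formula gives (24,150 − 48,300) / (483 − 1207.5) = −24,150 / −724.5 = +$33 per additional interpreted visit, which looks like an ordinary ratio.

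**Mobile video versus education.** Expected visits are equal, 2415 each. At 50% vs 55% the count difference turns negative only if mobile video has more than about 9% fewer visits (0.50 / 0.55 = 0.909), or roughly two of 23 providers' worth.

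**The case against.** Most of the opposing case bears on H4a, and much of it stands.

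- **Units.** A reader might infer that both ratios mix units. They do not. Dollars over interpreted visits is the right dimension for H4a, and with equal eligible visits the ratio is correct. The H4a weakness is missing standardization.
- **Main contrast.** H4a and H4b are hypothesized for mobile video against education. Those arms are randomized 1:1 with stratification by baseline use and clinic, so only chance imbalance in visit volume remains. The systematic wrong sign belongs to combination versus education.
- **Period.** The 2.5-to-1 imbalance depends on pooling phases 1 and 2. The Aim 1 and Aim 3 text supports that, but the sample-size paragraph places the group comparisons at the end of phase 2, where each group is expected to have about 966 visits. This removes the imbalance in expected size. It does not make the populations alike: in phase 2 the education group still includes its top tertile, and the combination group contains only lower users.
- **Model-based effects.** Because effectiveness is tied to Aim 1, which uses weighted GEE, raw counts may not be the intention. However, Aim 1 promises odds ratios, and the Aim 3 text specifies a difference in number.
- **Missing contrast.** A reader might infer that combination versus mobile video cannot be estimated. It can be obtained by subtracting the two stated contrasts once they share a base; it is simply not listed.

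None of this rescues H4b, where the stated target and the stated formula disagree on the page.

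**Conclusion.** H4b is wrong as written, and this needs no assumption: the ratio is a cost per 0-to-1 change in the proportion, too large by the number of patients or visits covered. On the plan's own denominators the factor is 216 (surveyed patients per group) or 1932 (visits per group). A reader might infer an error of three orders of magnitude. That holds only if all visits are taken as the base, and the documents do not fix the base. The dollar figures rest on the assumed $10,000.

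H4a is correct in unit but conditional: it is valid only with equal eligible visits. For mobile video versus education this holds in expectation. For combination versus education it fails if phases 1 and 2 are pooled, and the count difference is then negative unless combination use exceeds 2.5 times education use. That result assumes even attrition and 7 visits per provider per month; the negative counts shown also rest on assumed use rates.

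The formulas should be corrected before the Aim 3 analysis. The primary outcome, the design and the conduct of the trial are unaffected.

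**What to change.** Rewrite both definitions in the Aim 3 section:

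- ICER = difference in mean cost per eligible visit (or per provider-month) divided by the difference in the Aim 1 model-based probability of an interpreted visit (H4a) or of comprehension (H4b). If provider-months are used for cost, express the effect per provider-month too.
- Take cost and effect over the same period and the same provider population. For H4b, state that the probability comes from surveyed acute-visit patients and is being applied to the visits that generate the costs.
- For every contrast that involves the combination, restrict all compared groups in the same way, for example to re-randomized providers in phase 2. Restricting only the combination group would set lower users against all providers. The per-visit base is still needed there: among re-randomized providers about 966 combination visits face 23 / 3 × 63 = 483 in each continued single strategy.
- Report combination versus mobile video alone beside the two contrasts already listed.

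This needs no new data. The cost is slightly more analysis work and, for the combination contrasts, a result that applies to lower-use providers only.

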### Regulatory approvals

The mVOCAL Trial was registered on ClinicalTrials.gov on September 22, 2022 (NCT05591586). The Seattle Children’s Hospital institutional review board (IRB) serves as the single IRB (sIRB). The study was initially approved on October 29, 2021 (no. 00003332). All providers and patients will provide informed consent for their participation, with the exception of those participating only through the inclusion of their administrative data, for whom a waiver of informed consent has been obtained.

## Discussion

In this type 3 hybrid implementation-effectiveness study, we will test two discrete implementation strategies for improving professional interpreter use and patient comprehension in primary care. Using a SMART design will allow us to study the effect of the strategies alone and together mirroring the way a practice might implement a staged strategy, with additional intervention for providers with worse performance [64–66]. Given the different barriers targeted by the different strategies, we expect a greater response together, while a single strategy may suffice for many. Our SMART design, mixed methods, and inquiry into mechanisms will illuminate which provider and clinic characteristics would most likely benefit from each strategy, focusing on how, when, where, and why each is effective, rather than simply whether it is effective [115]. As both strategies are inherently scalable but not currently in widespread use, our study will provide actionable data to inform where and how to most effectively implement these strategies to improve safety and equity for patients who use a language other than English for medical care.

We will study these two implementation strategies without additional facilitation, in order to isolate the effect of each, as either could represent the minimum intervention needed to produce change (MINC) [116]. The MINC concept addresses the issue that many effective strategies are not widely adopted due to time and resource limitations in non-research settings. We will therefore test strategies that are relatively simple, with fewer barriers to real-world implementation, as they may lead to greater population impact through wide uptake, even if their individual effect is not as large as might be found for a complex intervention.

With provider-level randomization, contamination between groups is a concern; however, we do not believe it will undermine our ability to test our hypotheses for several reasons. First, we do not expect contamination with the mobile video interpreting strategy, as app access will be controlled by the study team, and we will request that providers not share mobile video interpreting-enabled devices with others. Second, we will measure mobile video interpreting contamination, as every mobile video interpreting use will be linked to a visit via billing invoices, and each mobile video interpreting account will be associated with a specific provider. Mobile video interpreting use at visits with nonmobile video interpreting providers will prompt an inquiry and remediating measures. Third, we will ask providers who are not assigned to the modules not to view them. It is possible that each strategy’s tip sheets may be printed and visible in shared clinic space. However, provider behavior is difficult to change, so we would not expect a minor exposure to meaningfully impact behavior [117]. Finally, we will explore possible contamination in provider qualitative interviews. Evidence of contamination would suggest we should interpret results with caution, but also that the implementation strategy could be widely adopted in practice.

The planned study will generate novel data regarding how effective each strategy is, under what circumstances, through which mechanisms, and at what cost. With these new data, healthcare organizations will be able to make informed decisions to best address the persistent communication-mediated inequities experienced by their patients with language barriers.

## Data Availability

Not applicable.

## Abbreviations

SMART: Sequential multiple assignment randomized trial
MINC: Minimum intervention needed for change
EMR: Electronic medical record
ED: Emergency department
TDF: Theoretical Domains Framework
COM-B: Capability, opportunity, motivation—behavior
PCP: Primary care provider
ICER: Incremental cost-effectiveness ratios
GEE: Generalized estimating equations
HIPAA: Health Insurance Portability and Accountability Act
